## Materials and methods

The current study protocol is designed to address the research questions described above via three protocol elements: (1) the Child Protocol, a set of behavioral tasks for children between the ages of 4–10 years; (2) the Parent Survey, a comprehensive survey to be completed by children’s parents or other primary caregivers; and (3) a Caregiver-Child Conversation task.

As described above, this study is currently being conducted in 39 distinct cultural-religious settings (to date), spanning 17 countries and 13 languages. All research teams aim to collect at least 40 children and their caregivers for each cultural-religious sample. Beyond this, planned sample size, eligibility, inclusion and exclusion criteria, recruitment strategies, the mode of data collection, and compensation vary across samples; these decisions are made by field site leaders in close consultation with the core leadership team. Sample-specific item selection also varies across samples, within the network-wide guidelines for each task that are detailed in the current manuscript. In addition to establishing these guidelines, this manuscript provides a detailed description of the adaptation and implementation of this protocol in the US, specifically within six cultural-religious samples: American Protestants, American Catholics, American members of the Church of Jesus Christ of Latter-day Saints, Jewish Americans, Muslim Americans, and religiously unaffiliated Americans. Future manuscripts will provide details of sample-specific design and sampling approaches for the other field sites and samples included in this research.

For the full text of all materials, all visual stimuli, and Qualtrics survey (.qsf) files, please visit https://osf.io/dumf4/.

### Samples

#### Sample size (US samples)

For each of the six US samples, we have set a planned minimum sample of 75 children (and their parents/caregivers) and a planned maximum sample of 100 children (and their parents/caregivers). The planned minimum of 75 reflects the largest minimum per sample we could imagine attaining given the US data collection staff and budget and the timing of this first wave of data collection (part of a three-wave longitudinal study, funded by a grant with an end date approximately 3 years after data collection began); the planned maximum of 100 reflects our estimation of a reasonable target goal given these practical constraints. This yields a total planned sample of 450 to 600 children. For each sample, our original plan was to stop collecting data when we have reached our planned maximum sample size, or on September 30, 2023, whichever came first; over the course of revising the current manuscript, we have encountered substantial difficulties recruiting participants from minoritized religious groups in the US (i.e., our Church of Jesus Christ of Latter-day Saints, Jewish, and Muslim samples), and have decided to extend the stop date to December 31, 2023. A sample is considered “complete” if it meets or exceeds the minimum sample size; if we do not meet that sample size by our end date, then any participants from the relevant group will only be included in analyses that pool across multiple samples.

(Please note that sampling plans vary substantially across the rest of the cultural-religious samples represented in the network, and will be provided in forthcoming manuscripts.)

#### Eligibility, inclusion, and exclusion criteria (US samples)

US samples are being recruited through the University of California, Riverside, and Boston University, using a shared set of eligibility, inclusion, and exclusion criteria.

To be eligible for inclusion, a family must currently live within driving distance of one of the two university campuses. Although data collection for Wave 1 in the US is remote due to the ongoing COVID-19 pandemic (see “Recruitment, data collection, and compensation [US samples],” below), this geographical restriction is intended to allow for in-person participation for future waves of data collection. Participating children must be between the ages of 4 years 0 months and 10 years 11.99 months at the time of the initial study session. Children must speak English or Spanish, and parents/caregivers must read and respond in writing in English or Spanish. Participating parents/caregivers must be parents or legal guardians of the participating child; multiple siblings from the same family are allowed to participate. Finally, parents/caregivers must report that children are either (a) being raised in one of the following religious traditions: Protestant Christianity, Catholicism, the Church of Jesus Christ of Latter-day Saints, Islam, or Judaism; or (b) being raised in no religious tradition (i.e., the child is religiously unaffiliated). Children who are being raised in other religious traditions (e.g., Buddhism, Hinduism, Orthodox Christianity, or Sikhism) are ineligible for the study; in these cases, families are thanked for their interest, and invited to participate in other studies in the relevant lab.

To determine which version of the study is most appropriate for each participating child, we ask parents/caregivers interested in participating in the study to complete an initial “Family Interest Form,” in which they respond to the following questions about their family’s religion: (1) “What is your religion, if any? Please be specific here by including any denomination(s), branch(es), or type(s) that you belong to, for example: Christian—Lutheran; Roman Catholic; Sunni Muslim; Shia Muslim; Orthodox Jew; Therevada Buddhist; Mahayana Buddhist; Not Religious—Agnostic.”; (2) “Does your child have the same religion (if any) as you?”; and, if the answer to the second question is no, (3) “What is your child’s religion, if any? Please be specific here by including any denomination(s), branch(es), or type(s) that your child belongs to, for example: Christian—Lutheran; Roman Catholic; Sunni Muslim; Shia Muslim; Orthodox Jew; Therevada Buddhist; Mahayana Buddhist; Not Religious—Agnostic”; and (4) “Which of the following religious and cultural traditions is your child most familiar with? You might take into account the religious background of other members of your extended family, or the religious traditions that are most common in your child’s neighborhood or school if your child is not religious.”

All religious children are given the version of the protocol that corresponds to the religion in which the parent indicates the child is being raised. Note that a child’s religious affiliation is assessed independently of their parents/caregivers’ religious affiliation(s). For example, if a parent indicates that he is Muslim (question 1), that the child does *not* have the same religion as him (question 2), and that the child is Protestant (question 3), then we consider this child Protestant for sampling purposes and the child is shown the Protestant version of the protocol.

When a parent/caregiver indicates that a child is being raised in *multiple* religious traditions, the child is shown the protocol corresponding to the religion with which the parent/caregiver says the child is most familiar, and these children are included in the sample for that religious group. Roughly halfway through data collection, we will assess how many mixed-faith children have been included in each cultural-religious group, and whether their responses diverge substantially from other participants. If so, we plan to replace these participants with new participants from families who report the child being raised solely or primarily in that religious tradition.

When a parent/caregiver indicates a child is religiously unaffiliated, the child is given the protocol version associated with the religious tradition most familiar to the child. If the parent/caregiver says that the child is not familiar with any religion and there are no religions mentioned in any other part of the Family Interest Form, the child is given the Protestant protocol; this reflects our understanding of Protestant Christianity as a pervasive cultural-religious force across US history, and the most common religious affiliation in the US through the present day [47].

In all cases–for religious children and for unaffiliated children–the parent/caregiver is given the version of the Parent Survey that matches the version of the protocol that the child has been given, regardless of the parent/caregiver’s own religious affiliation and familiarity with religion. We tell families that if there is one parent/caregiver whose religious affiliation (or familiarity with a specific religion) is more similar to the child’s, we would prefer that individual to complete the Parent Survey and Caregiver-Child Conversation.

The research team working in the US has adopted two exclusion criteria. First, children who do not appear to understand the majority of the Child Protocol, whose parents/caregivers frequently provide translations to the child in a language other than English or Spanish, or whose parents/caregivers spontaneously self-report concerns about their child’s comprehension, verbal expression, working memory, or other factors are excluded from the sample. Second, children whose sessions are frequently interrupted (e.g., by family members making suggestions about how the child should answer) are excluded from the sample; judgments of the frequency and severity of these interruptions are made by data collectors and discussed with other data collectors and supervisors from both universities (Boston University and the University of California, Riverside). We have no current plans to exclude data at the trial or task level, i.e., if a child’s data is included in the dataset our default will be to include all of their data. However, there might be some exceptions to this made on a case-by-case basis during regular meetings of the data collection team. All decisions regarding exclusion are made as a team with data collectors from both universities and at least one supervisor.

(Please note that eligibility, inclusion, and exclusion criteria vary substantially across the rest of the cultural-religious samples represented in the network, and will be provided in forthcoming manuscripts.)

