### Research questions

The inaugural members of the DBN undertook an interactive, collaborative process of drafting and revising the research questions that have guided study design for Wave 1. This initial round of data collection prioritizes the exploration of two broad topics of interest: the diversity of religious and supernatural concepts that children encounter, and the ways in which children come to understand and construct religiously-based social categories. For both topics, our goals are to uncover and describe children’s representations and reasoning, to chart age-related changes across early and middle childhood, to assess similarities and differences across cultural and religious settings, and to gain insight into the processes of social-cultural transmission that scaffolds children’s learning about how to think and act like the adults in their communities. The study covers a wide age range, to chart the developmental progression of religious cognition as well as to understand how children at their developmental level grapple with religion and the supernatural. These goals are articulated in three research questions detailed below.

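### Mixed-faith children may be replaced on the strength of their answers, so the data decide which population the five religious US samples represent

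*Protocol article*

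**What the plan says.** The rule is in the protocol article under Eligibility, inclusion, and exclusion criteria (US samples). A child raised in more than one tradition receives the protocol version for the religion that the parent calls most familiar, and "these children are included in the sample for that religious group". A second step follows: "Roughly halfway through data collection, we will assess how many mixed-faith children have been included in each cultural-religious group". At the same look the team will judge "whether their responses diverge substantially from other participants. If so, we plan to replace these participants with new participants". The new children are to be ones raised wholly or mainly in that tradition.

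The article names no task, statistic or threshold for the word substantially. The same section lists two formal exclusion criteria, poor comprehension and interrupted sessions, and neither mentions mixed faith. The article does not say whether replaced children stay in any analysis.

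On size, the Sample size (US samples) section says: "For each of the six US samples, we have set a planned minimum sample of 75 children" (with their caregivers) and "a planned maximum sample of 100 children". Under Research questions, one stated goal is "to assess similarities and differences across cultural and religious settings".

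**The concern.** Mixed-faith status is a fact about upbringing, reported by the parent. The plan accepts these children as eligible and tests them, and then lets their answers decide whether they stay. They remain if they resemble the other children and go if they do not. That is selection on the outcome.

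Two things are at stake:

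- **Target population.** A religious sample may end up describing all children raised in the tradition, or only those raised wholly or mainly in it. The interim data make that choice.
- **Description of variation.** The study sets out to describe diversity within and across settings. Research question 2 also includes a sub-goal on how religious identity relates to exposure to religious diversity. Children raised in two traditions bear directly on that sub-goal, and the rule removes them when they answer differently.

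**Working it through.** **Inputs from the article.** Each US sample has 75 to 100 children. Across six samples this gives 6 × 75 = 450 and 6 × 100 = 600, which reproduces the stated total of 450 to 600. A look at half of each sample falls at about 38 to 50 children. The article gives no figure for the rule itself.

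**Assumptions, not in the article.** Responses are standardised to SD 1. The mixed-faith share p is 10–30%. The true shift δ of mixed-faith children is 0, 0.5 or 1 SD. The cut-off is 0.5 SD on one measure.

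**1. Shift in the mean if all mixed-faith children are replaced.** The shift is p × δ. For δ = 0.5 it is 0.10 × 0.5 = 0.05 SD up to 0.30 × 0.5 = 0.15 SD.

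**2. Spread with everyone kept.** The SD is √(1 + p(1 − p)δ²).
- p = 0.2, δ = 0.5: √1.04 = 1.02
- p = 0.1, δ = 1: √1.09 = 1.044
- p = 0.3, δ = 1: √1.21 = 1.100

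**3. Chance that the rule fires with no true difference.** With m mixed-faith children among N at the look, SE(d) = √(1/m + 1/(N − m)). At a 20% share:
- N = 38, m = 8: SE = 0.398, and the probability that the absolute d exceeds 0.5 is 0.209
- N = 50, m = 10: SE = 0.354, probability 0.157

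**4. Simulation over the whole range** (4,000 runs per setting, with the number of mixed-faith children varying at random). The wording allows two readings. *Class*: all mixed-faith children, including later ones, are replaced if the observed difference reaches 0.5 SD. *Individual*: only those mixed-faith children present at the look who lie more than 1 SD from the mean of the others are replaced. Results for samples of 100, with the shift taken as negative:

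| Share | Shift | Class rule fires | Mean: all kept → class | SD: all kept → class | Mean, individual | SD, individual |
|---|---|---|---|---|---|---|
| 10% | 0 | 0.30 | 0.000 → 0.000 | 1.000 → 0.999 | −0.001 | 0.986 |
| 10% | 0.5 | 0.50 | −0.050 → −0.019 | 1.011 → 1.003 | −0.028 | 0.994 |
| 10% | 1 | 0.82 | −0.100 → −0.011 | 1.044 → 1.004 | −0.054 | 1.014 |
| 30% | 0 | 0.11 | 0.000 → 0.000 | 1.000 → 0.999 | 0.001 | 0.963 |
| 30% | 0.5 | 0.49 | −0.150 → −0.063 | 1.026 → 1.008 | −0.089 | 0.982 |
| 30% | 1 | 0.94 | −0.300 → −0.014 | 1.100 → 1.003 | −0.168 | 1.035 |

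Over samples of 75 and 100 and shares of 10%, 20% and 30%:
- **Class, no true difference:** the rule fires in 11–32% of runs, the mean stays unbiased, and the SD is 0.996–1.000.
- **Class, 0.5 SD shift:** the rule fires in about half of runs, yet on average 57–72% of the mixed-faith contribution to the mean is lost. More than half is lost because the rule fires when the observed difference happens to be large.
- **Class, 1 SD shift:** the rule fires in 74–94% of runs and 84–95% of the contribution is lost.
- **Individual:** the SD is 0.963–0.987 even with no true difference, and about 40–46% of any real shift is lost.

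**The case against.** The strongest reply is that the wording most naturally treats mixed-faith children as a class. On that reading, if they do not really differ, replacing them leaves mean and SD almost unchanged. If they do differ, the sample becomes children raised wholly or mainly in the tradition, which is a legitimate population. There is also a design reason to check. The Social Essentialism task sets a reference religion against a non-reference one, and a child raised in both may fit neither role. The rule is openly disclosed and conditional, and the study calls itself mostly exploratory.

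Much of this stands. It limits the size of the harm and shows that loss of spread is not certain. It does not rescue the mechanism: either population is defensible if chosen from parent report, but not if the responses choose it.

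A reader might infer more than the text supports:
- **That all six US samples are affected.** Mixed-faith children are placed in religious groups, so the rule reaches five samples and not the unaffiliated one.
- **That divergence on any one of the nine child tasks triggers replacement, making a false trigger nearly certain.** The article does not say this, and some tasks are open-ended with coding schemes not yet developed.
- **That each group is judged separately, so groups end up with different populations.** Only the count is described per group. Divergence might be judged on pooled data.
- **That differences between groups are inflated.** This would require mixed-faith children to lie toward the comparison group, and the article says nothing about direction.
- **That completed sessions are deleted.** The article says these children are replaced. It does not say what happens to their data.

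**Conclusion.** The point holds in a limited form. Membership of the five religious US samples depends on the outcomes to be analysed, and nothing else in the article withdraws the rule. If mixed-faith children truly differ, the rule tends to remove their contribution to the group mean and to within-group spread. If only divergent individuals are replaced, spread is understated even with no true difference. If the whole class is replaced and there is no true difference, the estimates are essentially unharmed, and what remains is a population chosen partly by noise.

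The numbers rest on the assumed share, shift and cut-off. At a 10% share and a 0.5 SD shift the effect on the mean is only 0.05 SD. General homogenisation of the samples, or exaggerated contrasts between religions, should not be claimed as established. This is a should-fix: the exploratory aims soften the consequence for hypothesis tests, but description is itself the primary goal.

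**What to change.** 1. Delete the response-based replacement rule.
2. Keep every enrolled mixed-faith child in the sample for the most familiar religion, as the article already provides.
3. Record mixed-faith status from parent report. The Family Interest Form questions shown in the article do not ask directly whether the child is raised in several traditions, so status may have to be coded from parents' free-text answers.
4. In every religious group, run the same analysis with and without all flagged children, whatever they answered.
5. If a limit on mixed-faith enrolment is wanted, base it on parent report only.
6. If the halfway look has already taken place, report what was examined and decided, and retain the replaced children's data.

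The cost is a paragraph of wording and one extra analysis per group. Recruitment effort is saved, because no replacements are needed, and the article reports difficulty recruiting in three of the five religious samples. The downside is that group estimates describe a somewhat more heterogeneous population.

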#### Recruitment, data collection, and compensation (US samples)

Participants are recruited through a combination of participant databases housed at the University of California, Riverside, and Boston University; targeted Facebook ads; community outreach; and personal outreach to religious leaders and organizations in the local areas surrounding the two campuses.

Given the ongoing COVID-19 pandemic and the high levels of access and exposure to computer technology, data collection in the US is being conducted entirely online. The Child Protocol is administered via live video chat between a researcher and the participating child. The session is recorded via Zoom (except in cases where the parent/caregiver or child declines to be recorded), and the researcher also logs most of the child’s responses in real-time via Qualtrics survey software. In some cases, the Caregiver-Child Conversation task is completed independently and asynchronously by parents/caregivers and children without live supervision by a researcher, and parents/caregivers submit an audio recording of this conversation to the research team via email. In other cases, the researcher administers the task to parents/caregivers and children at the end of the Child Protocol, or in a separate live video chat. Finally, parents/caregivers complete an online version of the Parent Survey independently and asynchronously via Qualtrics.

To thank participants, families are given one $20 e-gift card for each participating child upon completion of the Child Protocol, and an additional $20 gift card when the parent/caregiver completes the Caregiver-Child Conversation task and the Parent Survey. For families with more than one child participating, parents/caregivers receive an additional $10 gift card for completing the Caregiver-Child Conversation and Parent Survey with each additional child.

(Please note that recruitment, data collection procedures, and compensation vary substantially across the rest of the cultural-religious samples represented in the network, and will be provided in forthcoming manuscripts.)

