Each version of the protocol includes at least two *religious groups*, including the child’s own religious group or a locally prevalent religious group, as well as at least one other religious group salient in the local setting. These two religious groups are also featured later in the protocol in the Religious Indicators, Social Essentialism, Norm Violations, and Child as Transmission Agent tasks (described in later sections). For these two trials, the child is asked one additional follow-up question after the familiarity and reality status questions. If the child indicates that they are familiar with the group in question, the follow-up question is, “What do you know about [religious group]?” If the child indicates that they are not familiar with the group in question, the follow-up question is instead, “When I say the word(s) [religious group], what do you think of?”

Finally, each version of the protocol includes two agents intended as *attention/comprehension checks*: a novel category of entities presented in the plural generic (e.g., “Blambies”); and a novel entity presented as a singular individual (e.g., “The Rumber”).

All agents are presented in random order.

Research teams are encouraged to include a mix of specific individuals (e.g., “Santa Claus”) and plural generics (e.g., “zombies”), as relevant in the local language and cultural-religious setting. We do not specify which items should be worded in which way; in other words, we prioritize cultural specificity within a sample over syntactical standardization across samples.

Some research teams also include additional, sample-specific items in this list as desired, in order to capture aspects of the cultural-religious setting beyond what is captured by the standard list of agents. Additional items are randomized along with the other agents in the standard list, with the exception of any additional ethno-religious groups beyond the two described above, which are presented in a random order after the standard list.

In the US samples, this task is estimated to take 5 to 7 minutes with younger participants and 4 to 9 minutes with the oldest participants.

*Adaptation for US samples*. The final set of agents featured in the Sorting task for the five religions included in US samples is presented in Table 1.

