#### Norm Violations task: Assessing the perceived severity, alterability, and scope of religious norms relative to other norms (moral, conventional)

Building on previous work on children’s understanding of religious norms [e.g., 70–72], the Norm Violations task is designed to assess children’s familiarity with and reasoning about some of the most salient norms from their own religious group or a locally prevalent religious group, and to compare children’s judgments of violations of religious norms to violations of moral and conventional norms. This task is part of the Child Protocol; see Fig 2.

*Task design and procedure*. To introduce the task the researcher says, “Sometimes people do things that are okay and sometimes people do things that are not okay. I’m going to tell you about things that some people did, and I want you to tell me if you think those things were okay or not okay. If it’s okay, you can say ‘okay,’ or do this [*researcher demonstrates thumbs up*, *or another locally appropriate gesture*]. If it’s not okay, you can say ‘not okay,’ or do this [*researcher demonstrates thumbs down*, *or another locally appropriate gesture*].”

The child is then presented with two practice trials: The first focuses on an action that is clearly not okay (insulting someone), and the other focuses on an action that is clearly okay (giving someone a present). These practice trials are intended to familiarize children with the format of the task; to encourage them to use the full range of response options available to them; to encourage them to take the task seriously (i.e., provide sincere responses even if the questions seem silly or unusual); and to establish that the task might include both stories where characters do things that are “okay” and stories where characters do things that are “not okay.”

The main task consists of four blocks of questions presented in a random order.

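### US children are excluded on an unscored, unblinded judgement that they did not understand most of a largely religious battery, so exclusion may depend on the outcomes and fall mainly on the youngest

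*Protocol article*

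**What the plan says.** The section on eligibility, inclusion and exclusion criteria (US samples) excludes "children who do not appear to understand the majority of the Child Protocol". The same criterion also covers children whose caregivers often translate into a language other than English or Spanish, and children whose caregivers volunteer concerns about "comprehension, verbal expression, working memory, or other factors are excluded from the sample". No score, item set or threshold is attached to the comprehension judgement. On who decides, the section says: "All decisions regarding exclusion are made as a team with data collectors from both universities and at least one supervisor". By default, all data of an included child are used.

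The section on recruitment, data collection and compensation (US samples) states: "The Child Protocol is administered via live video chat between a researcher and the participating child". Sessions are recorded "except in cases where the parent/caregiver or child declines to be recorded", and the researcher logs most answers as they are given.

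Elsewhere the protocol contains material with an expected answer that does not depend on religion. In the Sorting task, "Finally, each version of the protocol includes two agents intended as" attention/comprehension checks (Blambies and the Rumber). The Sorting practice trials use doctors and a nonsense word. The Norm Violations practice pairs an insult with a present: "The first focuses on an action that is clearly not okay (insulting someone"). The Memory Span tasks have practice trials of their own. Neither the exclusion text nor the planned analyses of the Sorting task gives the two labelled checks a use.

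**The concern.** Of the nine child tasks, only Memory Span has no religious content. Several outcomes are themselves religious knowledge or fullness of answer: familiarity with agents (Sorting), recognising indicators of group membership (Religious Indicators), correct self-identification (Direct questions about religion), richer explanations (Justifications) and religious content (Child as Transmission Agent). A thin or confused performance on these tasks is both the data and the likely evidence for exclusion. The plan's own hypotheses expect younger children to do less well on them, so younger children are the likeliest to be removed.

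If the young children who remain know more than young children in general, age trends look shallower than they are. Main effects of age are planned for Sorting, Property Attributions, Direct questions, Justifications, Child as Transmission Agent and the Caregiver-Child Conversation. For Religious Indicators and Social Essentialism the planned age analyses are interactions, and for Norm Violations they are exploratory. Cross-sample comparisons could be affected too, but only if staff take unfamiliarity with religion for non-comprehension. An unaffiliated child who knows no religion still receives the Protestant version.

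The caregiver limb raises a related point: a volunteered concern about working memory excludes a child, although the Memory Span tasks are there to measure it.

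**Working it through.** The plan gives no exclusion rate, effect size or SD, so there is no figure of its own to reproduce. Everything below is illustrative and every parameter is an assumption.

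**1. Shift in the mean of the youngest.** Suppose a fraction p of 4-year-olds, those lowest on judged understanding, is excluded and almost no 10-year-olds are. Let judged understanding correlate ρ with the outcome, with both normal. The retained mean is then too high by ρ·φ(z_p)/(1−p) SD.

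| p | φ(z_p)/(1−p) | Shift, ρ = 0.3 | Shift, ρ = 0.7 |
|---|---|---|---|
| 10% | 0.195 | 0.06 SD | 0.14 SD |
| 15% | 0.274 | 0.08 SD | 0.19 SD |
| 20% | 0.350 | 0.11 SD | 0.25 SD |

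Against an assumed true difference of 0.8 SD between ages 4 and 10, 15% exclusion attenuates the age effect by 0.274 × 0.3 / 0.8 = 10% to 0.274 × 0.7 / 0.8 = 24%. A negative ρ would reverse the sign.

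**2. Simulation of age slope and group gap.** There were 400,000 simulated children per scenario, with age uniform from 4 to 11, standardised as a = (age − 7.5)/2.02, and half of them in a less exposed group (g = 1).
- General comprehension: C = 0.5a + N(0, SD 0.87).
- Religious outcome: K = 0.5a − 0.5g + 0.2C + N(0, SD 0.8). The full age slope is 0.5 + 0.2 × 0.5 = 0.60 and the full group gap is −0.50.
- Staff judgement: J = wK + (1 − w)C + N(0, SD 0.3), with the lowest q overall excluded.

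The weight w is 0 if the judgement tracks only general comprehension and 1 if it tracks only the religious outcome. Entries are the percentage of the full age slope / full group gap that is kept.

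| q overall | w = 0 | w = 0.5 | w = 1 |
|---|---|---|---|
| 2% | 98.8 / 100.1 | 95.5 / 97.1 | 94.3 / 93.4 |
| 5% | 97.8 / 100.0 | 91.0 / 94.8 | 88.7 / 88.4 |
| 10% | 96.4 / 99.9 | 85.2 / 92.0 | 81.6 / 81.6 |
| 15% | 95.4 / 99.5 | 80.7 / 90.2 | 75.5 / 76.5 |

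At 10% overall, about 22 to 25% of children under 6 were excluded, against 1 to 2% of those aged 9 or over. The age slope shrank in every scenario, by 1 to 24%. The group gap shrank by 3 to 24% when the judgement drew partly or wholly on religious knowledge, and essentially not at all when it did not. The percentages in steps 1 and 2 have different bases: the first is of 4-year-olds, the second of all children.

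**3. Could the two nonsense agents replace the judgement?** A child guessing at random passes both with probability 0.5 × 0.5 = 25%; a child who always says yes passes neither. Two items are too few to serve as the only rule.

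**The case against.** The strongest points against this are as follows.

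- **The decision is collective.** A reader might infer that whoever ran the session removes the child alone. The text does not support that: a team from both universities with at least one supervisor decides. This limits individual discretion, but it does not make the decision rule-based or blind.
- **Silence is not evidence of non-use.** A reader might infer that the built-in checks are ignored. The article does not say what evidence the team uses, and a manual may. What stands is that the stated rule gives the checks no role.
- **The tasks allow for unfamiliarity.** Answering no to a familiarity question is valid. Agents the child has not heard of are dropped from Property Attributions and Justifications, guessing is invited, and unknown words are skipped in the Direct questions. Ordinary people, gender, wealth, moral and conventional norms and memory games are also covered. Low religious knowledge alone need not look like failure to understand most of the session. This stands, and it is why the effect on sample differences is only conditional. No comparable skip is described for Religious Indicators, Social Essentialism, the Norm Violations blocks or Child as Transmission Agent.
- **The direction could differ.** Children who do not understand may say yes by default and raise the young children's scores, and removing them would then lower the mean. Attenuation is likely, not certain.
- **Religion-free items are imperfect.** Practice trials are training, memory-game practice is corrected by the researcher, and the insult/present pair resembles the permissibility outcome. This rules out using them as a sole test, not as supporting evidence.
- **The study describes itself as largely exploratory,** and excluding children who cannot follow a long interview is defensible. That lowers the stakes, but it does not tell readers whether age trends depend on who was removed.

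**Conclusion.** The point holds as a weakness in a stated rule. Whole children leave the sample on a judgement with no threshold and no stated blinding, made about a battery that is mostly outcome material. Exclusion may therefore depend on the outcomes, and the youngest are the most exposed.

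It would go too far to say that age and sample differences will be flattened. The documents give no exclusion rate, and the loss depends on that rate and on how far the judgement draws on religious answers. Under the assumptions shown, the age slope loses about 1 to 6% and the group gap at most about 7% at 2% exclusion. At 15%, both lose about a quarter if the judgement rests wholly on the religious outcome. If it tracks only general comprehension, the age slope loses at most about 5% and the group gap stays essentially intact. The change is worth making because it is cheap and would show which case applies.

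**What to change.** 1. Keep and flag the data of all children who completed a session, instead of dropping those judged not to have understood.
2. Report comprehension exclusions by age and by sample.
3. Repeat each planned age and cross-sample analysis with the flagged children included, as a sensitivity analysis.
4. Have the team record performance on the nonsense agents and other non-religious items as the primary supporting evidence for a comprehension exclusion, not as the sole pass/fail rule, and decide without reference to the content of the religious answers.

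The cost is a change of wording, a short record for each exclusion and one extra run per analysis. No new data are needed. The downside is noisier data from the youngest children in the sensitivity run.
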